## Abstract

**Background:**

Fundamental motor skills (FMSs) are crucial for children’s health and comprehensive development. Obese children often encounter a considerable challenge in the development of FMSs. School-family blended PA programs are considered a potentially effective approach to improve FMSs and health-related outcomes among obese children, however, empirical evidence is still limited. Therefore, this paper aims to describe the development, implementation, and evaluation of a 24-week school-family blended multi-component PA intervention program for promoting FMSs and health among Chinese obese children, namely the Fundamental Motor Skills Promotion Program for Obese Children (FMSPPOC) employing behavioral change techniques (BCTs) and building on the Multi-Process Action Control (M-PAC) framework as well as using the Reach, Effectiveness, Adoption, Implementation, and Maintenance (RE-AIM) framework for improving and evaluating the program.

**Methods:**

Using a cluster randomized controlled trial (CRCT), 168 Chinese obese children (8–12 years) from 24 classes of six primary schools will be recruited and randomly assigned to one of two groups by a cluster randomization, including a 24-week FMSPPOC intervention group and a non-treatment waiting-list control group. The FMSPPOC program includes a 12-week initiation phase and a 12-week maintenance phase. School-based PA training sessions (2 sessions/week, 90 min each session) and family-based PA assignments (at least three times per week, 30 min each time) will be implemented in the initiation phase (semester time), while three 60-min offline workshops and three 60-min online webinars will be conducted in the maintenance phase (summer holiday). The implementation evaluation will be undertaken according to the RE-AIM framework. For intervention effectiveness evaluation, primary outcome (FMSs: gross motor skills, manual dexterity and balance) and secondary outcomes (health behaviors, physical fitness, perceived motor competence, perceived well-being, M-PAC components, anthropometric and body composition measures) will be collected at four time-points: at baseline, 12-week mid-intervention, 24-week post-intervention, and 6-month follow-up occasions.

**Discussion:**

The FMSPPOC program will provide new insights into the design, implementation, and evaluation of FMSs promotion among obese children. The research findings will also supplement empirical evidence, understanding of potential mechanisms, and practical experience for future research, health services, and policymaking.

**Trial registration:**

Chinese Clinical Trial Registry; ChiCTR2200066143; 25 Nov 2022.

**Supplementary Information:**

The online version contains supplementary material available at 10.1186/s12889-023-15210-z.

## Contributions to the Literature

This study will guide future development, implementation and evaluation of FMSs promotion programs among obese children in the long runThis study will provide a paradigm of integrating theories and implementation strategies, adding values to future research and practice in health promotion among obese childrenResearch findings will supplement empirical evidence and practical experience for future implementation science on addressing FMSs, healthy lifestyles, and physical and mental health among obese childrenResearch findings will add more understandings of the underlying mechanism of FMSs development, contributing to future theory refinement, intervention design and policymaking

## Introduction

Fundamental motor skills (FMSs) are considered the building blocks for more advanced and complicated movements (e.g., games, sports, and recreational activities) that children will develop throughout their lives [1]. FMSs represent a degree of proficiency in a range of motor skills as well as underlying mechanisms such as motor coordination and control [1–3]. Commonly developed in childhood and subsequently refined into context- and sport-specific skills, FMSs can be categorized as three aspects: *locomotor skills* (e.g., running, jumping, and hopping), *object control/ball/manipulative skills* (e.g., throwing, catching, and dribbling), and *stability skills* (non-locomotor, e.g., balancing and twisting) [4, 5]. The mastery of FMSs has been purported as crucial elements of children’s physical, social and psychological development, which occurs in an orderly and sequential manner [6, 7]. Good FMSs may be the foundation towards a healthier life because of positive connections with physical activity (PA) [8–10], contributing to greater physical fitness [2, 4, 11], body weight status [12, 13], perceived motor competence [10, 14], sports engagement [15], cognitive function [16, 17], perceived well-being [18], and perceived quality of life [19].

Despite the important role of FMSs in children’s holistic development, obese children are usually confronted with an accelerated challenge in developing FMSs [20]. There have been numerous studies indicating that obese children were delayed in FMSs development and showed a prominently poorer performance of FMS tests compared with their peers with healthy weight [21–25]. This may be attributed to multifaceted factors. For example, large body mass index (BMI) can lead to excessive pressure to children’s skeletal system [26] and unfavorable changes in the major brain sites of neuroplasticity [27, 28], and decrease perceived motor capabilities [29], which subsequently inhibit the development of children’s FMSs. For obese children, poor FMSs may also weaken their motivation for engaging in PA and result in a low level of physical fitness, which in turn deteriorates adiposity status and causes a series of negative consequences for other health aspects, e.g., metabolic diseases, and mental disorders among children [30–32]. This vicious circle has been clearly illustrated in Stodden et al.’s model [33], which to some extent emphasizes the importance and necessity of promoting FMSs in obese children.

Traditionally, PA intervention programs have shown effectiveness in improving FMSs [32] and other health-related outcomes (e.g., physical fitness, cognition, and mental health) in overweight and obese children [34–36]. Schools are considered an ideal setting to implement PA interventions with the aim of promoting FMSs, as children spend most of their waking hours at school and schools can also provide better conditions (e.g., facilities, equipment, curriculum, health experts, peer support), easier access and maximum reach for intervention efforts [37, 38]. However, school-alone settings cannot address the large amount of out-of-school time (e.g., summer holidays) and parental influences that shape children’s behaviors in the home setting [39]. By contrast, family-based PA programs usually focus on the impacts of parents’ support, knowledge, attitudes, motivation, and other psychosocial factors towards children’s behaviors and emphasize the co-activity of parents and children to promote children’s FMSs development [37, 40, 41]. Previous studies have also provided evidence for the effectiveness of family-based PA interventions on improving children’s FMSs and healthy behavioral patterns [40, 41]. Nevertheless, for obese children, the development of FMSs requires more professional instruction and practice guided by qualified experts [3, 42], and this cannot be fully guaranteed in family-alone interventions. In addition, a social cooperative and interactive environment (e.g., at school) can facilitate a better development of FMSs, PA self-efficacy and social skills for obese children [43], while this cannot be fully achieved in a family-alone setting. Taken together, this suggests that a school-family blended PA intervention paradigm which can combine the merits of both school-alone and family-alone approaches, shows great potential in promoting FMSs and related health outcomes among obese children.

Notwithstanding the advocation of school-family integrated PA interventions, empirical evidence on obese children is still scarce, especially in China [44]. In addition, several limitations and research gaps of previous FMSs promotion programs should be further addressed. For example, previous studies show inconsistent findings in the intervention effect on balance among obese children [45, 46], which may be attributed to the lack of specific PA sessions that are tailored to promoting children’s balance in some studies [32]. Furthermore, the findings in terms of the long-term effects of PA interventions on obese children’s FMSs were mixed in previous studies [32]. Some studies indicated a sustained intervention effect of PA intervention on FMSs (e.g., at the 36-week follow-up assessment) [47], while others found that the increase in FMSs of obese children was not maintained during the follow-up, which even relapsed back to baseline levels [48–50]. The underlying reasons may be the absence of theory-based targets of interventions and Behavioral Change Techniques (BCT) that play a crucial role in maintaining the PA intervention effects in the long run [51, 52]. Moreover, the mechanisms of why the PA intervention successfully improved obese children’s FMSs have not been systematically examined in previous studies [53]. Identifying the mediation and moderation mechanisms of the intervention program is important and necessary, as it contributes to future design of effective FMSs promotion programs. In addition, previous studies have also shown a series of methodological limitations (e.g., lack of randomization and blinding, lack of objective standardized measures, lack of comprehensive evaluations for the intervention fidelity and quality) [32, 53], which may weaken the future implementation and generalization of the study findings.

To address the research and practice gaps, the present study aims to develop, implement, and evaluate a 24-week school-family blended multi-component PA intervention program for promoting FMSs and health among Chinese obese children, namely Fundamental Motor Skills Promotion Program for Obese Children (FMSPPOC). The particular objectives of outcome evaluation include: (1) examine the intervention effects of the FMSPPOC on improving the primary outcome (i.e., FMSs) among Chinese obese children; (2) examine the intervention effects of the FMSPPOC on improving the secondary outcomes (health behaviors, physical fitness, perceived motor competence, perceived well-being, M-PAC components, anthropometric and body composition measures) among Chinese obese children; and (3) identify the interrelationships between FMSs and physical and psychological outcomes (i.e., mediation mechanisms) and the moderating role of demographics.

## Method

### Study design

This study will apply a two-group double-blinded cluster randomized controlled trial (CRCT) with four measurement occasions, including baseline assessment (T0), mid-intervention assessment (T1: 12 weeks after the baseline assessment), post-intervention assessment (T2: 24 weeks after the baseline assessment), and follow-up assessment (T3: 48 weeks after the baseline assessment). Two groups include: 1) an intervention group (IG), receiving the FMSPPOC intervention for 24 weeks; and 2) a waiting-list control group (WCG), receiving the FMSPPOC intervention or relevant materials (based on participants’ requirements) after the completion of all data collection for IG (see Fig. 1). The design, implementation, and reporting of the FMSPPOC will follow the SPIRIT guidelines and the CONSORT statement [54, 55] (Supplement Material 1). The study protocol was approved by the Research Ethics Committee of Hebei Normal University (ref. No.2021LLSC051). This study was a key part of a large research project funded by the National Social Sciences Funding Committee of China (Ref. No.: 19200526).

**Fig. 1 Fig1:**
[figure not shown]
CONSORT flow diagram

### Participants

As childhood is a critical period for developing favorable FMSs that can continuously affect health and individual development in adolescence and adulthood, a health-promoting intervention that targets this age group is vitally important [56]. In pre-adolescence, neuroplasticity may be greater, changes faster based on experience [57, 58] and the brain may be particularly sensitive to the effects of PA when the brain's neural circuits are still developing [59]. Therefore, to address age-related declines in PA and maximize the benefits of PA on FMSs, obese children aged 8 to 12 years were selected as the target population for this study with obesity defined as a body mass index (BMI) at or above the 95^th^ percentile of the sex-specific BMI-for-age growth charts (https://www.cdc.gov/obesity/data/childhood.html).

#### Sample size estimate

An average medium effect size (Cohen *d* = 0.54) of PA intervention on FMSs in obese children was proposed based on previous studies [32]. Considering the minimal class size is 30 and the prevalence rate of childhood obesity is approximately 20% [60], a cluster size of 6 (for each class) was selected in this study. Using an ICC of 0.01 [61], an alpha of 0.05, a statistic power of 80%, and an attrition rate of 15% [43], at least 84 participants in each condition (12 clusters per condition), for a total of 168 participants in 24 clusters will be required for this CRCT.

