#### Recruitment and eligibility criteria

Based on the sample size estimate, this study is intended to recruit 24 classes from six primary schools (grades 2–5), excluding the private or special education schools or those participating in other PA-related programs. Using a random stratified sampling approach (e.g., socioeconomic status, geographical location, grade and class size of each school), six primary schools will be recruited in Shijiazhuang, Hebei, China. An invitation letter describing the study nature and participation requirement will be delivered to the principals of eligible schools. Upon the approval of the principals, one class from each grade will be randomly selected to participate in this study. All children in the selected classes will be provided with an informed pack comprising a plain language statement and a written informed consent form to be signed by their parents. The eligibility criteria will include: (1) aged 8–12 years; (2) Body Mass Index (BMI) greater than Chinese obesity cutoffs corresponding to 95th percentile of sex-specific and age-specific BMI reference standards [62]; (3) no previous substantial experiences in participating in FMSs-related promotion programs; (4) no prior diagnosis of physical, verbal, and cognitive disorders that may prevent participation in PA program and interrupt the outcome evaluation.

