#### Randomization and blinding

To avoid the potential for contamination, randomization will be conducted at the school level. All eligible schools will be randomly assigned to one of the two groups prior to baseline assessment, where each group will consist of three schools. Each school will select 28 obese children from four classes covering grades 2–5 to participate in this study, and the children in the same school will receive the same treatment. Randomization will be implemented with a ratio of 1:1, using the Excel software by a researcher who will not be involved in the participant recruitment, data collection or evaluation. Due the ethical concerns, participants are not able to be blinded as they will be informed with the study purpose and group allocation in the written informed consent form. Intervention facilitators and outcome evaluators will be concealed for the group allocation.

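### The sample size takes 6 obese children per class as the number available, yet its 84 per arm and 28 per school need 7 enrolled per class; the quoted 80% power does not hold with schools randomised.

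*Protocol article*

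**What the plan says.** The Sample size estimate section takes a standardised effect of 0.54 from previous studies. It bases the number of children per class on class size and prevalence ("Considering the minimal class size is 30 and the prevalence rate of childhood obesity is approximately 20" per cent), from which "a cluster size of 6 (for each class) was selected in this study". It adds an ICC ("Using an ICC of 0.01") and "an alpha of 0.05, a statistic power of 80%, and an attrition rate of 15" per cent. The result is "at least 84 participants in each condition (12 clusters per condition"), or 168 children in 24 clusters.

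Recruitment and eligibility criteria takes 24 classes from six schools, grades 2 to 5: "one class from each grade will be randomly selected to participate in this study". That is four classes per school. Randomization and blinding assigns whole schools, three per arm, and adds: "Each school will select 28 obese children from four classes". Table 3 repeats 168 children from six schools as the expected Reach.

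**The concern.** The section sets 6 children per class and ends with a total that implies 7 (84/12), and 28 per school from four classes is again 7. The step from 6 to 7 is not explained. It matters because the 6 is a count of who is there to be recruited, before refusals, the exclusion criteria and dropout. If 7 cannot be found in the sampled classes, a school either falls short or looks for children outside them, which departs from the stated sampling. The 80% power is also attached to 168 children in 24 class clusters, whereas six schools are what is randomised.

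**Working it through.** **Inputs.** From Sample size estimate: d = 0.54, ICC 0.01, alpha 0.05, power 80%, attrition 15%, class of 30, prevalence 20%, 6 per class. From Data analysis: two-tailed testing. From Recruitment and Randomization: four classes per school, three schools per arm.

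**1. Reproducing the stated N.**
- Individually randomised n per arm = 2 × (1.960 + 0.842)² / 0.54² = 53.8 (54.8 by the t-based calculation, rounded up to 55).
- Design effect = 1 + (6 − 1) × 0.01 = 1.05, giving 56.5 to 57.8.
- Attrition: divided by 0.85, 66.5 to 67.9, so 67 to 68 per arm.
- Whole classes of 6: 68/6 = 11.3, so 12 classes, or 72 per arm.

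The 12 classes reproduce; the 84 does not.

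**2. Where 84 may come from.** 6/0.85 = 7.06, or 7 per class. Then 7 × 12 = 84, 7 × 4 = 28 and 7 × 24 = 168. This matches every stated figure, but only if 6 is the number analysed.

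**3. Supply against quota.**

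| | Supply at 30 × 20% | Stated quota |
|---|---|---|
| Class | 6 | 7 |
| School (4 classes) | 24 | 28 |
| Arm (12 classes) | 72 | 84 |
| Total (24 classes) | 144 | 168 |

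The expected shortfall is 24 of 168 (14%) before consent and exclusions. Treating obesity as binomial with probability 0.20 and every class as 30, the chance of at least 7 in one class is 39%, of at least 28 in a school's 120 pupils 21%, and of at least 168 in all 720 pupils 1.6%.

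The plan gives no consent rate, so a range is assumed:

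| Consent | Expected total, classes of 30 | Average class needed for 7 |
|---|---|---|
| 100% | 144 | 7/0.20 = 35 |
| 90% | 130 | 7/0.18 = 39 |
| 80% | 115 | 7/0.16 = 44 |

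**4. Power.** Cluster-level t-test with k clusters per arm and m completers per cluster: noncentrality = 0.54 × √(km / (2 × DEFF)), DEFF = 1 + (m − 1) × 0.01, df = 2k − 2.

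| Cluster | Enrolled | m after 15% attrition | DEFF | df | Power |
|---|---|---|---|---|---|
| Class, k = 12 | 144 | 5.1 | 1.041 | 22 | 79.9% |
| Class, k = 12 | 168 | 5.95 | 1.050 | 22 | 85.3% |
| School, k = 3 | 144 | 20.4 | 1.194 | 4 | 54.5% |
| School, k = 3 | 168 | 23.8 | 1.228 | 4 | 59.5% |

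**The case against.** The best defence is that 6 means the analysed cluster size. With 6 analysed per class, a class-level t-test gives 77.9% power with 10 classes per arm and 82.1% with 11. Classes come in fours, so 11 becomes 12, and attrition applied once gives 7 recruited per class and 84 per arm. That route is coherent, so a reader who infers that 84 has no basis, or must count attrition twice, goes further than the document allows. It fails on one point: the section obtains 6 from class size times prevalence. That is the number expected to be present, and attrition can only reduce it.

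A reader might also infer that the target cannot be met even with full consent. The document does not support that. Thirty is the minimal class size and 20% is approximate; classes averaging 35 would supply 7 at full consent, and even at 30 a school has about one chance in five.

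Nor does the discrepancy mean that too few children are planned: 84 exceeds what the stated formula inputs require. It would be wrong to conclude that the target should be cut to 144, since that takes class-level power to 79.9% and school-level power from 59.5% to 54.5%.

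It is fair to say that most of the gap between 80% and these school-level figures comes from the unit of randomisation. Six against seven per class accounts for about 5 points.

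**Conclusion.** The point stands as an inconsistency between the sample-size and recruitment figures. The stated inputs lead to 67 to 68 per arm, or 72 in whole classes, not 84, and the plan's own supply figure does not yield the 7 per class on which 84, 28 and 168 depend. The discrepancy in N is conservative and by itself biases no estimate. The practical consequence is a quota that is not expected to be met if classes are near 30: 144 against 168 at full consent, fewer after refusals and exclusions. This rests on 20% prevalence, classes at the stated minimum and binomial variation; larger classes would remove it.

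Separately from the head count, 80% power is not delivered with three schools per arm. It is about 59% with 168 and 54% with 144, assuming that the stated ICC of 0.01 applies at school level, 15% attrition and a t-test on 4 df.

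**What to change.** Use one set of figures in Sample size estimate and in Randomization and blinding, and carry it to the Reach row of Table 3. Either of two wordings would do:

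- State 7 recruited and 6 analysed per class, and give the average class size and consent rate that supply 7 (for example 35 at full consent, or about 44 at 80%).
- Enrol every eligible, consenting child in the 24 classes with no fixed 28 per school; give 144 as the expected yield at the minimum class size before refusals and exclusions, and keep 168 as the aim if larger classes allow.

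In either case, replace the 80% with power computed with the school as cluster, stating the number of schools, the degrees of freedom, the ICC and the attrition used. The cost is rewording of two paragraphs and one table entry, with no added enrolment.

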### Data analysis

Quantitative data analyses will be performed using SPSS and Mplus. Descriptive statistics of all continuous variables will be expressed as mean ± standard deviation (*M* ± *SD*). Independent samples *t*-tests and Chi-square tests will be employed for checking the randomization, analyzing the dropout, and detecting the potential confounders at baseline. Intention-to-treat approach will be used for the primary analyses, with per-protocol analyses as sensitivity tests. Missing data will be imputed using a multiple imputation approach with linear and logistic regression equations. The statistical significance level will be set to *p* < 0.05 (two-tailed). Generalized linear mixed models (GLMM) will be used to evaluate the intervention effects on outcome measures, with time, condition, and the interaction of time and condition as fixed effects, adjusting for baseline values. Post-hoc tests will be conducted where a significant interaction effect is detected by using the least significant difference method. In addition, structural equation modeling will be used to analyze the interrelationship (e.g., mediation mechanisms) of outcomes, using a bias-corrected bootstrap approach (5000 resamples). For the qualitative data, a thematic analysis approach will be applied using NVivo 11 software.

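### The sample size counts 24 classes as clusters, but only six schools are randomised, so the stated 80% power does not belong to this design

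*Protocol article*

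**What the plan says.** Under Sample size estimate, the protocol assumes a standardised effect of 0.54, an ICC of 0.01, alpha 0.05, 80% power and 15% attrition. On the cluster it says "a cluster size of 6 (for each class) was selected in this study", and it concludes that "at least 84 participants in each condition (12 clusters per condition), for a total of 168 participants in 24 clusters will be required".

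Under Randomization and blinding, the unit is different: "randomization will be conducted at the school level", "where each group will consist of three schools". Each school contributes 28 obese children from four classes, and all children of a school receive the same treatment.

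Under Data analysis, tests are two-sided at 0.05. Outcomes are analysed with a generalized linear mixed model "with time, condition, and the interaction of time and condition as fixed effects", adjusted for baseline values.

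**The concern.** Since the four classes of a school are never split between arms, classes are not independent units for the comparison of arms. The randomised unit is the school. Counting 24 clusters instead of six affects the calculation in two ways. The design effect must use about 24 to 28 children per cluster rather than 6. And the comparison has 6 − 2 = 4 between-school degrees of freedom rather than the 22 that 24 classes would suggest.

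The power for the primary outcome, fundamental motor skills, is at stake. An analysis that respects the randomisation has less power than stated. An analysis that takes over the sample size section's view of the cluster would produce p-values that are too small.

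**Working it through.** **Inputs from the protocol.** d = 0.54, alpha 0.05 two-sided, ICC 0.01, attrition 15%, class size 6 and 12 classes per arm (Sample size estimate; sidedness from Data analysis). Three schools per arm and 28 children per school (Randomization and blinding).

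**Assumptions added here.** The ICC of 0.01 applies to schools; the protocol ties it to no school-level source, so a range is shown. Condition is tested with a t statistic on 4 df. No gain from baseline adjustment is counted at first, because the sample size section claims none.

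**1. The plan's own figure, class as cluster**
- Per arm without clustering: 2(1.96 + 0.84)²/0.54² = 53.8, so 54.
- Design effect: 1 + (6 − 1)(0.01) = 1.05; 54 × 1.05 = 56.7.
- Attrition: 56.7/0.85 = 66.7, so 67 per arm; 66.7/6 = 11.1, so 12 classes.

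The 12 clusters reproduce. The 84 children do not follow directly: 12 × 6 = 72, whereas 84/12 = 7 per class. (Inflating 72 again for attrition gives 72/0.85 = 84.7, but the protocol does not describe that route.) If classes were independent, 84 per arm would give 71.4 completers and power of 88% by the normal approximation, or 85% on 22 df.

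**2. The design as randomised, school as cluster**
- Completers per school: 28 × 0.85 = 23.8; per arm 3 × 23.8 = 71.4.
- Design effect: 1 + (23.8 − 1)(0.01) = 1.228.
- Effective n per arm: 71.4/1.228 = 58.1.
- Noncentrality: 0.54 × √(58.1/2) = 2.91.
- Critical t on 4 df: 2.776. Power from the noncentral t: **59.5%**.

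| School ICC | Design effect | Noncentrality | Power, t on 4 df | Power, normal approximation |
|---|---|---|---|---|
| 0 | 1.000 | 3.23 | 67.9% | 89.7% |
| 0.01 | 1.228 | 2.91 | 59.5% | 82.9% |
| 0.02 | 1.456 | 2.67 | 52.8% | 76.2% |
| 0.05 | 2.140 | 2.21 | 39.3% | 59.7% |

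The d detectable with 80% power on 4 df is about 0.70 at ICC 0.01. It scales with the square root of the design effect, so at ICC 0.05 it is 0.70 × √(2.140/1.228) = 0.92.

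**3. Where the loss comes from**

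At ICC 0.01 the larger design effect alone leaves 82.9% by the normal approximation. Replacing 1.96 by the 4-df t distribution takes it to 59.5%. Most of the loss therefore comes from having three randomised units per arm.

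**4. Baseline adjustment**

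The baseline–follow-up correlation r is not given. Multiply the variance by (1 − r²) and keep 4 df:

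| r | Power at ICC 0.01 | Power at ICC 0.05 |
|---|---|---|
| 0 | 59.5% | 39.3% |
| 0.5 | 71% | 49% |
| 0.7 | 86% | 64% |
| 0.8 | 94% | 78% |

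**5. If clustering were ignored altogether**

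The actual type I error of a nominal 5% test is 2Φ(−1.96/√DE), with DE the design effect above. At ICC 0.01 it is 2Φ(−1.77) = 7.7%; at ICC 0.05 it is 2Φ(−1.34) = 18%.

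**The case against.** Three objections carry weight.

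**The planned analysis is baseline-adjusted.** This stands. A reader might infer that no ICC could give 80% power, or that a null result is likely even if the assumed effect is real. The documents do not support either as a general statement: both hold only for an unadjusted comparison. At ICC 0.01 and r = 0.7, power exceeds 80%. But the sample size section neither claims this gain nor states a correlation, so it does not rescue the figure as written, and at ICC 0.05 even r = 0.8 falls just short.

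**The 60% rests on a school ICC and a 4-df test that the protocol does not state.** This stands as a qualification. The section pairs 0.01 with a class cluster, and the true school ICC could be lower or higher. The mismatch of unit does not depend on it, and without baseline credit power is 68% even at ICC 0. A design effect with the normal approximation gives 83%, which looks adequate, but that approximation is not reliable with six clusters.

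**The model may already handle schools correctly.** A reader might infer from the list of fixed effects that school will be ignored. The text does not say so. A mixed model has random effects by definition, and a condensed article may leave their structure to the analysis plan. The inflated type I errors are therefore the consequence of a mistake to avoid, not of a stated analysis.

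**Conclusion.** The point holds as a contradiction between two sections of the protocol. The calculation is for 24 class clusters; the trial randomises six schools. The 80% power claim cannot stand as written.

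The size is conditional. With d = 0.54, two-sided alpha 0.05, 15% attrition, a school ICC of 0.01, 4 df and no baseline credit, power is about 60%, with a range of 68% to 39% over ICC 0 to 0.05. With baseline adjustment it could be on either side of 80%, depending on the school ICC and the correlation. The protocol gives neither quantity for the unit that it randomises.

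**What to change.** Reconcile Sample size estimate with Randomization and blinding:

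- Restate power and detectable effect with the school as cluster: 3 per arm, 28 recruited per school, 4 df, over a range of school ICCs such as 0 to 0.05.
- If baseline adjustment is to be credited, state the assumed correlation and its source, and quote power with and without it.
- Correct the class size in the same paragraph: 84 per arm in 12 classes is 7 per class, not 6.
- State, in the protocol or the analysis plan, that the mixed model has a random intercept for school and that condition is tested with small-sample degrees of freedom (for example Kenward-Roger or Satterthwaite), so that school is treated as the randomised unit.

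This costs a rewritten paragraph and one sentence on the model. The stated power will be less favourable, but no extra children are needed. If the sponsor would rather keep about 80% power without relying on baseline adjustment, four schools per arm of the same size give 79.9% at ICC 0.01 (t on 6 df). That would be a change of design, not of wording.
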